## Study background

Challenging behaviours can include physically, verbally or sexually aggressive, destructive or self-injurious behaviour (van den Akker et al. 2020). The estimated prevalence of challenging behaviour problems in intellectual disabilities in large population studies shows considerable variation between 4–22% (Bowring et al. 2019), with multiple factors likely to underlie challenging behaviours in this population.

Results of a meta-analysis of risk factors associated with challenging behaviours in people with intellectual disabilities indicate that men with intellectual disabilities are significantly more likely to show aggression than women, and that individuals with severe/profound intellectual disabilities are significantly more likely to show self-injury and stereotypy than individuals with mild/moderate intellectual disabilities (McClintock et al. 2003). Individuals with a diagnosis of co-occurring autism are significantly more likely to show self-injury, aggression and disruption to the environment whilst individuals with deficits in receptive and expressive communication are significantly more likely to show self-injury, but overall, the meta-analysis highlighted the paucity of methodologically robust studies of risk markers for challenging behaviours in populations with intellectual disabilities (McClintock et al. 2003).

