## Definition of the study population

Data on all patients with intellectual disabilities will be acquired from CPRD. Individuals with intellectual disabilities will be identified using Read codes in Appendix 1. Co-occurring challenging behaviours will be defined as a binary variable (present or not) based on READ codes in Appendix 1. Patients registered in a practice between January 1 January 2009 and 31st December 2019 will be included in the study. We require that their practice allows linkage to HES, MHSDS and IMD data, resulting in the inclusion of English practices. Patients who are registered at CPRD practices not participating in the linkage scheme, or who have individually opted out, will not be included.

Earliest cohort entry date will be 1/1/2009. Patients who register after 1/1/2009, or who are diagnosed with intellectual disabilities during the study period, will be followed from that date. Patients will be censored if they transfer out from their CPRD practices, or opt out before the end of the study period (31/12/2019). However, challenging behaviour diagnoses of patients who leave a CPRD practice prior to the end of the study period will be included in a sensitivity analysis.

Index case for a case would be one of the following:

- 1/1/2009 (if a patient is actively registered on this date with a diagnosis of challenging behaviours prior to 2009)
- date of diagnosis (if a patient's date of first diagnosis of challenging behaviours is after 1/1/2009 while they are registered)
- date of registration (if a patient's date of registration is after 1/1/2009 and they have a prior diagnosis to that registration)

Inclusion criteria:

- all patients with intellectual disabilities (as defined in READ codes in Appendix 1) registered at a general practice for at least six months prior to cohort entry date
- patients who receive a diagnosis of intellectual disabilities after cohort entry date and have a valid registration status for at least six months

Exclusion criteria

- patients registered at practices not participating in the linkage scheme, or who have individually opted out

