### **Phase 1**

We will calculate the incidence of challenging behaviours within the group with intellectual disabilities. Our binary outcome will be defined on the basis of having a record of a relevant Read code for co-occurring challenging behaviours (Appendix 1). Records will be stratified by age, sex, severity of intellectual disabilities and/or co-occurring physical conditions/autism/genetic syndromes/mental comorbidities if cell sizes allow. Tables of baseline characteristics will be described for all patients with intellectual disabilities. For continuous data, mean, median, range, and standard deviations will be calculated. For categorical variables, frequency and percentages will be reported.

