### **Phase 2**

The main statistical analyses will be conducted using stratified Cox proportional hazard models (Sjolander & Greenland 2013). The Cox models will be run univariately, then multivariably. The multivariable analysis will comprise (i) adjustment for demographic (age, gender, ethnicity) and socioeconomic (Practice/Patient Level Index of Multiple Deprivation) factors, (ii) the addition of mediators (i.e. severity of intellectual disabilities, co-occurring autism/genetic syndromes/mental comorbidities) factors) to the above model to assess any attenuation in the associations (iii) the use of likelihood ratio tests to test for interaction effects with the effect modifier (i.e. physical conditions including pain, sleep problems, constipation, epilepsy, urinary/bowel incontinence and sensory impairments) if there is sufficient statistical power and if found to be statistically significant, further sub-group analyses. We will test for proportional hazards in the Cox models using both graphical methods and a formal statistical test based on Schoenfeld residuals. Where the assumption of proportional hazards is violated, we will augment the models with time varying covariates. To account for patients with multiple events over the 10-year study period and investigate incidence rate ratios, we will conduct a Poisson regression, similarly to the methodology applied by Sheehan et al. (2015).

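### The Poisson regression named for repeat challenging-behaviour events has no stated within-patient variance correction, so its rate-ratio intervals would be too narrow if patients differ in underlying rate

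*Protocol*

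**What the plan says.** The protocol's Phase 2 section sets the order of the analyses. The Cox models come first: "The main statistical analyses will be conducted using stratified Cox proportional hazard models". The repeat-event analysis closes the section: "To account for patients with multiple events over the 10-year study period and investigate incidence rate ratios, we will conduct a Poisson regression". The same sentence adds that this will resemble the method of a cited UK cohort study of mental illness, challenging behaviour and psychotropic prescribing in people with intellectual disability. No variance estimator, random effect, overdispersion check or alternative count model is named there or elsewhere in the protocol.

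The outcome is defined twice, both times as present or absent. Definition of the study population has: "Co-occurring challenging behaviours will be defined as a binary variable (present or not) based on READ codes in Appendix 1". Phase 1 has: "Our binary outcome will be defined on the basis of having a record of a relevant Read code". Neither place says when a second code in the same patient is a new event.

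Two other sections bear on whether patients differ in underlying rate. Study background lists risk markers, among them: "individuals with deficits in receptive and expressive communication are significantly more likely to show self-injury". Communication deficits do not appear among the covariates in Exposures, outcomes and covariates. Limitations of study design acknowledges that coding differs between practices and over time.

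**The concern.** Poisson regression is brought in for one purpose, to deal with patients who have several events. It does half of that job, because it lets every event contribute to a rate. It does not deal with dependence. The model-based standard error rests on the variance of a patient's count being equal to its mean, given the covariates. If some patients have a persistently higher rate for reasons outside the model, their events cluster, the variance exceeds the mean, and the standard error is too small.

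At stake is the precision claimed for the incidence rate ratios. Intervals would be too narrow, and too many null associations would be declared significant. Data/statistical analysis says that all analyses are repeated in each subgroup, so the shortfall would recur there. The large cohort does not help, because the understatement is a ratio that does not shrink as patients are added.

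The missing rule for a new event matters for the same reason. If repeat records of one problem were counted as separate events, within-patient clustering would grow.

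**Working it through.** **The plan's own figures.** Sample size considerations gives 81,529 patients with intellectual disabilities and 13,452 with challenging behaviours. Both reproduce: 0.005 × 16,305,791 = 81,528.96 and 0.165 × 81,529 = 13,452.3. They do not settle this point. The 16.5% is a prevalence on a given day, not a rate of coded events. The protocol gives no event rate, dispersion or standard error for the Poisson model, so the inputs below are assumptions.

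**Inputs (assumed).** Mean events per patient, μ: 0.2, 0.5 and 1.0. Variance of a multiplicative patient effect with mean 1 that remains after covariates, k: 0, 1, 2 and 4.

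**Formulas.** With such an effect, Var(Y) = μ + kμ², while the Poisson model assumes Var(Y) = μ. Hence

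- true SE ÷ Poisson SE = √(1 + kμ)
- real two-sided error of a nominal 5% test = 2 × [1 − Φ(1.96 ÷ ratio)]

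| μ | k = 0 | k = 1 | k = 2 | k = 4 |
|---|---|---|---|---|
| 0.2 | 1.00; 5.0% | 1.10; 7.4% | 1.18; 9.8% | 1.34; 14.4% |
| 0.5 | 1.00; 5.0% | 1.22; 11.0% | 1.41; 16.6% | 1.73; 25.8% |
| 1.0 | 1.00; 5.0% | 1.41; 16.6% | 1.73; 25.8% | 2.24; 38.1% |

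Each cell shows the SE ratio and the real error rate. For example, √(1 + 1 × 0.2) = 1.10 and √(1 + 4 × 1.0) = 2.24. Over k = 1 to 4, nominal 95% intervals cover between 92.6% and 61.9%.

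**Simulation check.** 2,000 patients, 30% exposed, follow-up uniform from 0.5 to 10 years, log follow-up as offset, true rate ratio 1, gamma-distributed patient effect, 500 runs:

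| μ | k | Poisson SE | Robust SE | Actual SD of estimate | Error, Poisson | Error, robust |
|---|---|---|---|---|---|---|
| 0.5 | 0 | 0.069 | 0.069 | 0.068 | 4.8% | 4.6% |
| 0.5 | 1 | 0.069 | 0.088 | 0.083 | 9.2% | 4.2% |
| 0.5 | 2 | 0.069 | 0.104 | 0.101 | 18.2% | 4.0% |
| 0.5 | 4 | 0.069 | 0.129 | 0.126 | 28.2% | 4.4% |
| 1.0 | 2 | 0.049 | 0.091 | 0.089 | 30.2% | 3.4% |

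The Poisson standard error does not react to k, whereas the robust one follows the actual spread. Unequal follow-up makes the SE ratio somewhat larger than the formula gives. For follow-up uniform on 0.5 to 10 years, μ is in effect multiplied by (5.25² + 9.5²/12) ÷ 5.25² = 1.27. At μ = 0.5 and k = 2 the ratio becomes √(1 + 2 × 0.636) = 1.51, which matches 0.104 ÷ 0.069. With 500 runs, the error rates carry a Monte Carlo standard error of about 1 to 2 percentage points.

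**The case against.** Four points can be made against the concern.

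1. The sentence defers to a cited study whose variance method is not visible here, and an analysis plan may exist. Either could supply a robust or mixed-model variance. This stands in part. A reader might infer that an uncorrected Poisson model will certainly be run, and the document does not establish that. It does establish that the protocol names the model for a stated purpose and states no correction. A general resemblance to another study's method does not state one either.

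2. Variance options are usually left to an analysis plan, and Poisson regression with robust errors is still Poisson regression. This limits the weight of the point. It does not remove it, because the protocol presents the named model as what accounts for multiple events, and that model's default standard errors do not do so.

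3. The size comes from assumed inputs, and stratification and adjustment would absorb some heterogeneity. This stands. The residual amount cannot be derived from the protocol, and with k = 0 nothing is lost. Zero is unlikely, given an unmodelled risk marker and the acknowledged variation in coding. The covariate list in Phase 2 is tied to the Cox models, so how far it carries over to the Poisson model is not stated.

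4. The binary definitions serve presence and Phase 1 incidence, and are not offered as a counting rule. This is correct. A reader might infer that every repeat code will be counted as an event, but no section says so. What can be said is that the rule is absent.

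A reader might also infer that patients with physical conditions consult more, collect more repeat codes and so have inflated rate ratios. Nothing in the protocol supports that. It would be a bias in the estimate, which a variance correction would not cure, and it forms no part of this point.

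**Conclusion.** The point holds for the precision of the incidence rate ratios in the additional repeat-event analysis. Followed as written, with default standard errors, that analysis understates uncertainty wherever residual between-patient heterogeneity exists. Across the assumed range the understatement runs from slight (about 7% error) to serious (about 38%). The direction follows from the model, but the size is conditional on assumptions that the protocol cannot confirm.

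It would be wrong to extend this to the study's main results. The Cox models are the stated main analysis and are untouched. This is a correction worth making before the repeat-event analysis is run, not a flaw in the design.

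**What to change.** Amend the last sentence of Phase 2 along these lines: *Repeat events will be analysed by Poisson regression with robust standard errors clustered on patient, with log person-years as offset.* Negative binomial regression with the same offset is an acceptable alternative. The offset should be written out because entry is staggered and patients are censored at different times.

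Add a sentence stating when a further challenging-behaviour code counts as a new event. If a code-free gap is used, its length is for the investigators to choose and to vary in a sensitivity analysis. If the cited study's method already includes a within-patient correction, say which one rather than rely on the reference.

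The first-event Cox models remain the main analysis. The cost is two sentences and somewhat wider confidence intervals. If there is no residual heterogeneity almost nothing is lost: in the simulation with k = 0 the Poisson and robust standard errors were both 0.069.

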## Feasibility counts

Records on all eligible patients with intellectual disabilities between the period of 1 January 2009 and 31 December 2019 will be analysed. The feasibility of identifying patients with intellectual disabilities in CPRD data has been successfully tested in previous research (Carey et al. 2016; 2017; Glover et al. 2019; 2020).

Carey et al. (2016) searched for any code used by the NHS Primary Care Quality and Outcomes Framework for learning disability and codes for conditions usually associated with intellectual disabilities (as is planned in the current project), such as chromosomal and metabolic disorders. This approach identified 21,859 adults (aged 18 years) registered in 451 English practices for at least 1 day between 1 January 2009 and 31 March 2013. The cross-sectional analysis reported on a subset of 408 practices that were providing high-quality data on 1 January 2012. A total of 14,751 people with intellectual disabilities aged 18–84 years who had been registered for at least 30 days on the 1 January 2012 date were included, along with 86,221 matched controls. Since our study will have a longer follow-up time (1 January 2009–31 December 2019) and will include patients with intellectual disabilities of all ages as opposed to adults only as has been done in Carey et al. (2016), we expect our sample size to be larger and, thus, have sufficient statistical power.

In the second study by Carey and colleagues (2017), 21,859 adults with intellectual disabilities, registered during 2009–13, were initially identified using an extended list of Read codes for intellectual disabilities and associated conditions. Specific analyses were based on smaller subgroups of adults with intellectual disabilities: a cross-sectional analysis of health and health-care quality on 1 January 2012 ( $n = 14,751$ ), a longitudinal analysis of mortality and hospital admissions during 2009–13 ( $n = 16,666$ ) and individual health checks ( $n = 7,510$ ). Since our study will have a longer follow-up time (1 January 2009–31 December 2019) and will include patients with intellectual disabilities of all ages as opposed to adults only as has been done in Carey et al. (2017), we expect our sample size to be larger and, thus, have sufficient statistical power.

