### Sample size considerations

As per details provided in the 'Feasibility counts' section, if we assume a 0.5% prevalence of intellectual disabilities as per findings reported by Glover et al. (2019; 2020) using a CPRD GOLD database with a follow-up period of April 2010-March 2014, then within the population of currently registered research acceptable (de-duplicated) patients (N=16,305,791 in total; N=3,020,680 for GOLD database and N=13,285,111 for Aurum database) 81,529 patients would be expected to have intellectual disabilities on any given day. Prevalence studies of challenging behaviours in nationwide primary care samples are lacking, but if we assume that a prevalence of challenging behaviours in a population of people of all ages with intellectual disabilities in England is as described in a study of seven District Health Authorities in the UK by Emerson et al. (2001), 16.5% (N=13,452) of patients with intellectual disabilities are expected to have any form of challenging behaviours on any given day during the study follow-up period of 2009-2019, with prevalence rates for specific types of challenging behaviours expected to be much higher (e.g., 42.0% for aggressive behaviours). Given the estimated sample size, the study is expected to have sufficient statistical power. References after amendments: Emerson, E., Kiernan, C., Alborz, A., Reeves, D., Mason, H., Swarbrick, R., Mason, L., & Hatton, C. (2001). The prevalence of challenging behaviours: A total population study. *Research in Developmental Disabilities*, 22(1), 77-93.

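### The protocol relies on Poisson regression to account for repeat events without saying how within-patient correlation and overdispersion are handled; with model-based standard errors the rate-ratio intervals could be too narrow.

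*Protocol*

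**What the plan says.** Under Phase 2 the protocol gives the primary role to time-to-event models: "The main statistical analyses will be conducted using stratified Cox proportional hazard models". Checks for these are spelled out: graphical methods, a test based on Schoenfeld residuals, and time-varying covariates where proportionality fails.

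The section closes with the repeat-event analysis: "To account for patients with multiple events over the 10-year study period and investigate incidence rate ratios, we will conduct a Poisson regression". The same sentence says that this will be done along the lines of a cited UK cohort study. It names no variance estimator, patient effect, alternative count model or check for overdispersion, and the rest of the statistical section and the missing-data plan name none either.

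Phase 1 defines the outcome as present or absent: "Our binary outcome will be defined on the basis of having a record of a relevant Read code for co-occurring challenging behaviours". No rule says what counts as a second event in the same patient. The opening of the data analysis section says that all analyses will be repeated in each subgroup.

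**The concern.** The protocol identifies a feature of the data, several events in one patient, and names Poisson regression as the means of accounting for it. That is only half an answer. A Poisson model lets a patient contribute more than one event and divides by time at risk, but its model-based standard errors are right only if the variance of the counts equals their mean, given the covariates. Coded challenging behaviour is likely to depart from that: most patients will have no event, and a minority may have several.

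This is the only planned analysis that uses more than the first event, and the only one said to give incidence rate ratios. If its standard errors were too small, some rate ratios for physical conditions would look more precise than they are. The excess of false positives would recur across the several conditions and across subgroups.

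**Working it through.** **The plan's own figures.** The protocol states no events per patient, dispersion or standard error. Its only related numbers are under Sample size considerations, and they reproduce:

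- Source population: 3,020,680 + 13,285,111 = 16,305,791.
- With intellectual disabilities: 16,305,791 × 0.005 = 81,528.96, stated as 81,529.
- With challenging behaviours: 81,529 × 0.165 = 13,452.3, stated as 13,452.

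The 16.5% is described as holding on any given day. It is a point prevalence, not a cumulative share and not an event rate, so it does not determine phi.

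**Effect of a given phi.** If variance = phi × mean, the correct standard error is sqrt(phi) times the model-based one. Coverage of a nominal 95% interval is then 2Φ(1.96/sqrt(phi)) − 1. All phi values below are assumptions.

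| phi | model-based width as % of correct width | coverage |
|---|---|---|
| 1.0 | 100% | 95.0% |
| 1.1 | 95% | 93.8% |
| 1.5 | 82% | 89.1% |
| 2 | 71% | 83.4% |
| 3 | 58% | 74.2% |
| 5 | 45% | 61.9% |
| 10 | 32% | 46.5% |

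**What phi might be.** Suppose a share p of patients has any event, with a mean of m events each, and follow-up is equal. Assume p = 0.165, borrowing the point prevalence as a proxy.

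*Lower bound, whatever the distribution.* Since E[N²] ≥ pm², the variance is at least pm² − p²m². Dividing by the mean pm gives phi ≥ m(1 − p). This exceeds 1 once m > 1/0.835 = 1.2.

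- m = 1.5: phi ≥ 1.25, coverage at most 92%.
- m = 2: phi ≥ 1.67, coverage at most 87%.
- m = 3: phi ≥ 2.50, coverage at most 78%.
- m = 4: phi ≥ 3.34, coverage at most 72%.

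*Geometric counts among those affected (an assumption).* E[N²] = p(2m² − m), so phi = 2m − 1 − pm.

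- m = 1: 2 − 1 − 0.165 = 0.835. Model-based intervals are slightly too wide.
- m = 1.09: about 1.0. No problem.
- m = 1.2: 1.20, coverage about 92.6%.
- m = 2: 2.67, coverage 77%.
- m = 3: 4.50, coverage 64%.
- m = 4: 6.34, coverage 56%.

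These are marginal ratios; covariates in the model would absorb part of the excess.

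**Simulation under a different assumption.** Each run had 4,000 patients, 30% exposed, no true effect, variable follow-up with a log person-time offset, and gamma heterogeneity between patients with variance k around mean count mu. There were 400 runs per setting.

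| mu | k | coverage, model-based | coverage, robust |
|---|---|---|---|
| 0.165 | 1 | 89% | 93% |
| 0.165 | 5 | 83% | 94% |
| 0.5 | 5 | 67% | 95% |
| 1 | 5 | 55% | 96% |

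The direction agrees with the formula, and robust errors bring coverage back close to nominal. The size depends entirely on the assumed mu and k.

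**The case against.** The best defence is that the protocol nowhere commits itself to model-based standard errors. A Poisson regression with patient-clustered errors is still a Poisson regression, so one of the remedies proposed here fits the text as it stands. The sentence also points to a cited study whose methods may include such a step, and a statistical analysis plan that is not shown may settle it. The choice of variance estimator is commonly left to that document. All of this stands, which is why the point is conditional. It does not remove the point, because the protocol does more than leave a detail open: it presents the model itself as the solution to repeat events, and the model alone is not one.

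A reader might also infer that the intervals will be far too narrow however an event is defined. The documents do not support that. They give no events per patient, and by the formulas above the problem vanishes when affected patients average close to one event. A strict new-episode rule could bring that about. The definition of an event, which the protocol leaves open, therefore governs the size.

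Finally, the repeat-event model is one closing sentence after the Cox models. It would be wrong to read the point as a doubt about the main hazard ratios.

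**Conclusion.** The point holds in a limited, conditional form. As written, the protocol's means of accounting for multiple events covers counts and person-time but not within-patient correlation or overdispersion. If default standard errors are used, intervals for the incidence rate ratios are too narrow by sqrt(phi). On assumed values that ranges from hardly noticeable (phi 1.1) to less than half the correct width (phi 5). With 16.5% as a proxy for the share of patients with any event, some overdispersion is certain, before covariates, once those patients average more than about 1.2 events. That proxy, equal follow-up and every value of m, mu, k and phi are assumptions, not figures from the protocol.

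The effect is confined to the supplementary repeat-event analysis and its repetition in subgroups. The documents do not show that model-based errors will be used, or that the shortfall in coverage will be large. The change is still worth making, because it costs almost nothing and does no harm if dispersion proves small.

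**What to change.** In Phase 2, state that the repeat-event model will be either a Poisson regression with standard errors clustered on the patient or a negative binomial regression, with log person-time at risk as offset, and that the estimated dispersion will be reported. State also what counts as a separate event in the same patient, since this determines how much the choice matters. If the cited study's method already includes such a step, name it in the protocol instead of relying on the citation.

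The cost is one option in the regression command and a sentence or two of text. No new data are needed. Intervals may become wider, to the extent that the data are overdispersed.
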